### Sample size

The sample size computation is based on studies conducted in similar populations, testing the efficacy of electronic interventions. The sample size was computed for the primary analysis: evaluation of intervention effects at 6 months on the number of drinks per week (past 30 days). Considering results reported by our group on an Internet-based brief intervention study conducted in Switzerland [5, 6], the sample size required is 551 individuals per group to demonstrate a significant difference with power of 90% and α type I error of 5%. Considering the potential need to adjust for clustering (recruitment on four sites with hypothetical low intraclass correlation of rho = 0.001) and an attrition rate of 10%, 848 participants per group are needed (771 + 77). A total of 1696 individuals is therefore the minimum number to be included.

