**Methods:**

This is a parallel-group, randomized controlled trial (1:1 allocation ratio) among 1696 university students with unhealthy alcohol use, identified by screening and followed up at 3, 6, and 12 months. Participants will be randomized to receive access to a smartphone-based intervention or to a no intervention control condition.

The primary outcome will be self-reported volume of alcohol drunk over the past 30 days, reported as the mean number of standard drinks per week over the past 30 days, measured at 6 months. Secondary outcomes will be number of heavy drinking days over the past 30 days, at 6 months. Additional outcomes will be maximum number of drinks on any day over the past 30 days, alcohol-related consequences (measured using the Short Inventory of Problems (SIP-2R), and academic performance.

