### Recruitment procedure

All students registered at the participating higher education institutions are provided a university/school email address once they are admitted. The participating institution will send an email presenting the study to all students. The study will be presented as a repeated survey of students’ alcohol use, in which participants could be asked to consult prevention material on their smartphone. Because higher education institutions in Switzerland welcome numerous international students, the study will be available to those speaking French and English. Students interested in participating will be directed to a specifically developed study website. On the study website, students interested in participation will complete a screening questionnaire assessing inclusion criteria. The screening will be anonymous and no personal data will be recorded at this point. The questionnaire will include the AUDIT-C, a validated screening questionnaire (including the online version) on unhealthy alcohol use, with differing cut-off scores by gender [10, 32].

Individuals fulfilling the inclusion criteria will receive a description of the study, indicating the follow-up schedule and assurance of confidentiality. Interested potential participants will be directed to complete an online consent form and asked to provide a physical address, an additional email address (at which to be contacted in case they leave the University/school during the study period) and a mobile phone number. They will then receive an email with a unique identifier linking to the baseline questionnaire. Only participants completing the baseline assessment will be included in the trial. Upon completion of the baseline questionnaire, participants will be randomized to one of two groups to receive: (1) assessment + access to personalized smartphone application (intervention condition) or (2) assessment only (control condition). Participants in the control condition will not receive access to the app.

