### Statistical analyses

The primary analysis will answer the main research question: “Is providing access to a smartphone app effective in reducing drinking compared to a no-intervention control condition?” The primary analysis will be to compare the intervention and control groups at 6 months on the primary outcome measure: the volume of alcohol drunk reported as the mean number of drinks per week over the past 30 days. All available data will be used in an intent-to-treat paradigm (i.e. individuals will be analyzed according to their initial group allocation). Missing values will be handled through a multiple imputation procedure in order to respect the intention-to-treat paradigm [28]. The null hypothesis is that both conditions have comparable effects on the volume of drinking at the 6-month follow up. The alternative hypothesis is that participants in the intervention group (experimental condition: secondary prevention intervention) will report a smaller volume of drinking at the 6-month follow up compared to participants in the control group.

Count models will be used. Because we are expecting that the data will not be normally distributed, an adequate count model will be selected by comparing different count models. From previous studies conducted with the same outcome, we expect a negative binomial regression model to best fit the distribution of the sample [5, 6]. If this is confirmed, the impact of the intervention will be assessed by a random-effects negative binomial model for mean number of drinks per week. The model will specify subject and recruitment site as random effects and intervention and time as fixed effects (with a time * intervention interaction term). The model will be adjusted for age and gender.

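### The sample size adds a cluster-randomisation inflation (551 to 771 per group) to a trial that randomises individual students, so 1696 is not the minimum for 90% power on the plan's own basis

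*Protocol article*

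**What the plan says.** The protocol article's Sample size section builds the total in three steps.

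- **Base:** "the sample size required is 551 individuals per group to demonstrate a significant difference with power of 90% and α type I error of 5" per cent. The inputs come from an earlier Internet-based brief intervention study by the same group. The article prints no effect size or dispersion and does not say whether the test is one- or two-sided.
- **Clustering and attrition:** the allowance is introduced with "Considering the potential need to adjust for clustering (recruitment on four sites with hypothetical low intraclass correlation of rho = 0.001"), followed by "an attrition rate of 10%, 848 participants per group are needed (771 + 77").
- **Conclusion:** "A total of 1696 individuals is therefore the minimum number to be included".

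On the design, the abstract describes a "parallel-group, randomized controlled trial (1:1 allocation ratio) among 1696 university students". The Recruitment procedure section states: "Upon completion of the baseline questionnaire, participants will be randomized to one of two groups". The Randomization section confirms that the study website allocates each participant automatically after baseline.

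On the analysis, the Statistical analyses section states: "The model will specify subject and recruitment site as random effects". Intervention, time and their interaction are fixed effects. No random site-by-intervention effect is specified.

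**The concern.** Attrition accounts for the separate 77, so the whole step from 551 to 771 is the clustering allowance. An inflation of about 40% at rho = 0.001 is what one obtains when whole sites are the unit of allocation. In that design a site's own level of drinking falls entirely on one arm and adds to the variance of the comparison.

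In this trial students at every site can enter either arm. A site's level of drinking is shared by both arms and drops out of the difference between them.

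What is at stake is the justification of the sample size. The number called a minimum for 90% power belongs to a different design, and the power of the trial actually planned is not stated. Anyone judging recruitment against 1696 would be using the wrong benchmark for the stated power target.

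**Working it through.** **Inputs from the protocol article:** 551 per group, 90% power, alpha 5%; four sites, rho = 0.001; 10% attrition; 771, 848 and 1696; 1:1 individual randomisation. **Assumptions made here:** a two-sided test, a normal approximation, and 551 taken as correct because it cannot be rebuilt from the printed text.

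**1. Reproducing the plan's figure.** The implied inflation is 771/551 = 1.399. Setting 1 + (m − 1) × 0.001 = 1.399 gives m = 400, and 551 × 1.399 = 770.8, which rounds up to 771. The article states neither this formula nor m; both are inferred. Other natural choices come close:

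| Cluster size m | Design effect | n per group |
|---|---|---|
| 1542/4 = 385.5 | 1.3845 | 763 |
| 400 | 1.399 | 771 |
| 1696/4 = 424 | 1.423 | 785 |

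The remaining steps add up: 771 + 77 = 848, and 2 × 848 = 1696.

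**2. The factor that applies.** With individual randomisation and both arms at each site, the variance factor is about 1 − rho = 0.999, so no inflation is needed.

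**3. Requirement without the inflation.** 551/0.9 = 612.2, so 613 per group and 1226 in total. Adding 10% instead of dividing by 0.9, as the article does, gives 607 per group and 1214 in total. The difference from the stated total is 1696 − 1226 = 470, or 28% of 1696.

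**4. Power of the planned trial.**
- Standardised difference that 551 per group detects with 90% power: (1.960 + 1.282) × √(2/551) = 0.195.
- Completers per group: 848 × 0.9 = 763.
- Power: Φ(0.1953 × √(763/2) − 1.96) = 96.8%. A one-sided 5% test, with its own implied difference, gives 96.4%.
- A simulation with 763 per arm, four sites, rho = 0.001, individual randomisation and an unadjusted test (20,000 replicates) gave power of 0.970, for equal and for very unequal site sizes.

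**5. Sensitivity to the role of site.**

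| Situation, 763 completers per group | Design effect | Power |
|---|---|---|
| Shared site effect only (the planned model) | about 1 | 96.8% |
| Independent site-by-arm effects, rho = 0.001 | 1 + (763/4 − 1) × 0.001 = 1.190 | 93.8% |
| Whole sites randomised, two per arm | 1 + (763/2 − 1) × 0.001 = 1.381 | 90.1% |

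Only the last row returns the stated 90%. That supports the inference that the calculation was made for allocation by site.

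**The case against.** The strongest reply is that the text is hedged. It speaks of a potential need and a hypothetical correlation, which reads as a safety allowance and not as a claim that sites are randomised. The allowance also enlarges the trial: it causes no bias, no inflation of the type I error and no loss of power. Both observations are fair, and they keep the matter from being serious. The hedge does not carry through to the conclusion, though, which says that 848 per group are needed and that 1696 is the minimum. Nor does possible heterogeneity between sites rescue the figure: independent site-by-arm effects at the stated rho give a factor of about 1.19, not 1.40.

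Other parts of the reply stand in full.

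- A reader might infer that the true power is 97%. The document does not support that. The figure depends on 551, whose effect size and dispersion are not printed and come from a study of a different, Internet-based intervention. As an illustration, if the real standardised effect were 15% smaller (√(551/763) = 0.85), power with 763 completers per group would be back at 90%.
- A reader might infer that the target should be cut to 1226. With the same 15% smaller effect, 1226 would give about 79% power, so the margin has value even though its stated reason is wrong.
- A reader might infer that a shortfall would trigger needless extension of recruitment. Nothing in the article ties extension, stopping or interpretation to reaching 1696.
- A reader might infer that site should become a fixed effect. That is a modelling preference and has no bearing on this calculation.

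**Conclusion.** The point holds as a misapplied design factor; the article's additions are internally consistent. The step from 551 to 771 per group does not belong to an individually randomised trial whose model has no random site-by-intervention effect, and 1696 is not the minimum for 90% power.

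On the plan's own basis the requirement is about 1226, and 1696 gives about 97% power, or about 94% with independent site-by-arm effects at rho = 0.001. These figures rest on 551 per group giving 90% power, a two-sided 5% test and 10% attrition. The cluster size of about 400 is inferred. Stratification of the randomisation by site is not stated and is not needed for the argument.

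The error is conservative and leaves the validity of the trial intact. It is a correction to the justification and does not threaten the result.

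**What to change.** Keep 1696. In the Sample size section, remove the cluster design effect as the reason for the number, and remove the word minimum. State that 1696 gives about 97% power after 10% attrition under the assumptions behind 551 per group.

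If the allowance was meant as a margin for site-by-intervention heterogeneity, say so, give the heterogeneity assumed and derive the inflation from it.

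The random site effect in the model can stay as it is. The cost is the rewording of one paragraph, with no change to recruitment, conduct or analysis.

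### The 10% attrition allowance is added to the 771 needed, not divided out, so 848 per group absorbs about 9.1% loss; the effect is minor and no definite power loss follows

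*Protocol article*

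**What the plan says.** The Sample size section of the protocol article builds the trial size in three steps.

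- Base: "the sample size required is 551 individuals per group", chosen "to demonstrate a significant difference with power of 90% and α type I error of 5" per cent.
- Clustering: an allowance for "recruitment on four sites with hypothetical low intraclass correlation of rho = 0.001". The result, 771 per group, appears only inside the next step. No cluster size or design effect is printed.
- Attrition: "an attrition rate of 10%, 848 participants per group are needed (771 + 77".

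The section then concludes: "A total of 1696 individuals is therefore the minimum number to be included". The same total is given as the trial size in the Methods part of the Abstract ("randomized controlled trial (1:1 allocation ratio) among 1696 university students with unhealthy alcohol use") and again under Participants.

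**The concern.** An attrition rate is a share of those randomized. If a fraction d is lost and n must remain, the number to enrol is n/(1 − d). The article uses n × (1 + d), which always falls short of that. Here the step is printed, so nothing has to be inferred about how 848 arose.

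What is at stake is internal consistency. A total described as a minimum does not follow from the inputs given beside it, and the figure is repeated as the size of the trial. The trial report will have to restate this calculation, so an uncorrected slip is likely to carry over. Whether the power is also affected has to be checked separately.

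**Working it through.** **Inputs, all from the Sample size section:** 551 per group for 90% power at 5% alpha; four sites, intraclass correlation 0.001; 771 per group after clustering; 10% attrition; 848 per group; 1696 in total. Effect size, variance, sidedness of the test and cluster size are not given. The attrition check needs none of them.

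**1. Reproducing the plan's figure.** 771 × 0.10 = 77.1, so 771 + 77 = 848, and 2 × 848 = 1696. The printed figure is n × (1 + d).

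**2. What 848 delivers at 10% loss.** 848 × 0.90 = 763.2 per group (1526 in total), against 771 (1542 in total). That is about 8 completers short per group.

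**3. Attrition that 848 can absorb.** 1 − 771/848 = 0.0908, or 9.1%.

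**4. Enrolment that leaves 771 after 10% loss.** 771/0.90 = 856.7, so 857 per group and 1714 in total. Difference: 9 per group, 18 in total; 18/1696 = 1.1%.

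**5. Does power fall below 90%?** Scaling from the plan's own base of 551, with a two-sided 5% test assumed, power = Φ[(1.960 + 1.282) × √(n_eff/551) − 1.960]. Here n_eff is the number of completers divided by the design effect 1 + (m − 1) × 0.001, and m is the cluster size. Since m is not stated, two assumptions are shown.

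*(a) Cluster size fixed.* The implied design effect is 771/551 = 1.3993, which means m of about 400 per site (551 × 1.399 = 770.8). Held fixed:
- n_eff = 763.2/1.3993 = 545.4
- power = Φ(1.265) = 89.7%. A one-sided test also gives 89.7%.

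*(b) Four equal sites, both arms counted, shrinking with the completers.*
- m = 1526.4/4 = 381.6
- design effect = 1 + 380.6 × 0.001 = 1.3806
- n_eff = 763.2/1.3806 = 552.8, just above 551
- power = about 90.1%

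Under (b), the number needed solves n = 551 × [1 + (n/2 − 1) × 0.001], that is n = 551 × 0.999/(1 − 0.2755) = 759.8, or 760 per group. So 763 completers suffice.

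Unequal sites would raise the design effect. Counting clusters by site and arm would lower it: m = 1526.4/8, about 191, and a design effect of about 1.19. The article does not settle which applies.

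**The case against.** Four points can be made for leaving the figure alone.

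- **Follow-up may be better than 10% loss.** The Follow up section cites 91% at 6 months in an earlier study by the same group, and 848 × 0.91 = 771.7, which just meets 771. This suggests the practical shortfall may not occur. It does not repair the calculation, because the planning assumption stated beside 848 is 10%.
- **Missing values will be multiply imputed** (Statistical analyses). This keeps everyone in the intention-to-treat set but does not recreate unobserved 6-month outcomes. The 3-month data may recover a little information. The plan itself inflates for attrition, so it does not rely on imputation to cover it.
- **The clustering inflation may be generous.** Randomization is by individual, and the article calls the adjustment only a potential need. Against the unclustered 551, 763 completers is a surplus of about 38% (763/551 = 1.385), and any power concern would vanish. This stands as a reason to treat the point as minor.
- **1696 is called a minimum**, so it is a floor and not a cap. That is true, but the stated floor is still not the one its inputs give.

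The opposite over-reading is also tempting. A reader might infer from 763 being less than 771 that the trial misses its 90% power, at 89.7%. The article does not support this. That figure requires a cluster size of about 400 per site, which is back-solved from 771/551 and then held constant while the completers fall. With four equal sites that shrink with the completers, the same 763 give slightly more than 90%.

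**Conclusion.** The attrition step is wrong as printed. At the stated 10% loss, 848 per group leaves about 763 completers, not 771, and 848 absorbs 9.1%. This rests only on figures in the Sample size section. Rounding explains at most 1 of the 9 per group.

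The consequence is minor: 1.1% of enrolment. No definite loss of the stated 90% power should be claimed, since power is about 89.7% or about 90.1% depending on an unstated cluster size. Nothing here threatens the validity of the trial.

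**What to change.** Correct the sentence in the Sample size section in one of two ways.

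- Keep 1696 and describe what it provides: 771 analysable per group at about 9% attrition, or 763 at 10%.
- State that 10% attrition requires 771/0.90 = 857 per group, 1714 in total, and align the Abstract and Participants sections with that total.

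If the clustering allowance is revised, apply n/(1 − 0.10) to whichever analysable number is kept. The first option costs one sentence and no extra enrolment; the second adds 18 participants. Neither changes the outcome, model or analysis set.

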### Monitoring

Monitoring will be performed according to the International Council for Harmonisation of Technical Requirements for Pharmaceuticals for Human Use (ICH) Good Clinical Practice (GCP) by the Clinical Trial Unit, Lausanne University Hospital and University of Lausanne. The monitors will follow a monitoring plan to verify that the clinical trial is conducted and that data are generated, documented, and reported in compliance with the protocol, GCP, and the applicable regulatory requirements.

### Ethics

The study, its methods and design, has been approved by the Commission Cantonale d’Ethique de la Recherche sur l’Etre Humain, Vaud (CER-VD) (no 2018–00560).

## Conclusion

This trial is aimed to close the evidence gap on the efficacy of smartphone-based secondary prevention interventions. As of today, evidence on Internet-based interventions for unhealthy alcohol use is available [49], but it is mostly lacking on smartphone interventions, even though this research area has been the focus of more research efforts in recent years [55].

A notable strength is the content and design of our intervention, which is theoretically based and is informed by pilot studies and previous experiences from our group with respect to electronic interventions. From a study design perspective, information technology allows for adequate randomization, concealment of allocation, and blinding. Electronic interventions are also more consistent.

One limitation, the absence of biological measures of alcohol use, should be acknowledged. It was not included for practical reasons, as collecting biological samples in the study sample was not achievable with the available resources. In addition, common biologic measures have poor sensitivity for low-level unhealthy alcohol use. Another potential limitation is the potential for repeated assessments to lead to a reduction in drinking (i.e. assessment reactivity), by initiating a reflection on one’s own alcohol use [38]. Nevertheless, the use of electronic assessments should limit social desirability bias or the Hawthorne effect [39].

### Potential impact and dissemination of results

If proven effective, smartphone-based interventions have the potential to reach a large portion of the population, completing what is available on the Internet. By relying on existing resources within universities or higher education institutions, this trial has the advantage of testing a procedure that could be widely implemented outside a research trial, without significant additional resources (beyond the maintenance of the application). It also targets a population with a high prevalence of unhealthy alcohol use, who suffer significant consequences of unhealthy alcohol use. If proven effective, the application will be made freely available. In accordance with the Swiss National Science Foundation guidelines, the study results will be published in open access publications. Results will also be communicated to the participating universities and higher education institutions.

## Data Availability

Data will be made available in accordance with the Swiss National Science Foundation open access and data sharing rules and recommendations.
